### Research Questions

1. Do youth (12 to 17 years of age) who engage in the 6-month HELP e-intervention have a larger improvement in emotional health (measured by the Strengths and Difficulties Questionnaire) than youth who do not receive the intervention?
2. Does engagement in the HELP e-intervention improve lifestyle behaviour (physical activity, sleep or screen time)?
3. Are changes in emotional health and lifestyle behaviours sustained for at least 6 months after completion of the HELP e-intervention?
4. Do youth who engage in the 6-month HELP e-intervention utilize fewer mental healthcare resources, during and for 1 year following RCT participation, than youth who do not receive the intervention?
5. Do mental health professionals supporting youth who engage in the 6-month HELP e-intervention provide lifestyle behaviour support less frequently than for youth who do not receive the intervention?
6. Are self-reported (i.e., perceived) lifestyle behaviour changes (study questionnaire responses) aligned with objective measures of screen time (smartphone tracking) and sleep and physical activity (accelerometry) in a randomly selected sub-sample (1 of 3) enrolled participants?

We hypothesize that youth engaging in the HELP e-intervention will have improved emotional health and enhanced lifestyle behaviours in comparison to those receiving the delayed (post 6-months) intervention. We hypothesize that changes during the intervention will be maintained for an additional 6 months, and that self-reported measures will accurately reflect objective measurements. We hypothesize that youth engaging in the HELP e-intervention will require fewer youth mental health supports, and when supported will be less likely to require treatment directed at lifestyle behaviours.

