## Study Procedures/Evaluations

### Recruitment

The primary avenue for recruitment will be via 1Call1Click. During our pilot study of the HELP e-intervention (REB #21 85X) we developed a best practice advisory flag within EPIC (Appendix A) that was provided to 1Call1Click intake staff if the youth met the age criteria for the research study. Youth who access 1Call1Click have an initial assessment by intake staff. Staff have information about the research study and have been educated regarding the inclusion/exclusion criteria. If the research study could be appropriate for the patient, the intake staff will ask the patient/family if they would like more information about research. If the response is positive, intake staff will send an EPIC inbasket message to the research team who will follow up with the patient/family to discuss the study details.

During the pilot study we also received feedback from youth, families and clinicians requesting that the HELP e-intervention be more widely available to youth who are at various stages in their journey to mental wellness. Therefore, additional youth may be recruited through our two secondary recruitment options. CHEO mental health clinicians will be able to refer youth for enrollment in the research study if they have obtained permission from the youth to do so. This avenue for recruitment will enable youth on the wait list for specialist support or who are currently receiving CHEO support to be eligible for study recruitment. We will also distribute the study information via posters (Appendix B) and social media posts (Appendix C) in CHEO patient areas and through our youth partner groups (CHEO Youth Forum, CHEO-RI Family Leader Program, YouthNet / R$é$seau Ado, the study’s Lived Experience Advisory Group, etc.). Youth who contact the research team after viewing the study information will also be eligible to enroll.

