The research coordinator will collect the healthcare system impact outcomes via medical chart review after participants have completed the 12-month assessment. For the 18 months after study enrollment, we will record the number and type of youth mental healthcare system contacts (request for support, appointment scheduling, treatment visit). We will also track the number, type (e.g., community provider, peer support, outpatient, day treatment, inpatient), purpose (assessment, counselling), professional seen (e.g., psychiatrist, psychologist, social worker, nurse) and length (visit length in minutes) information for each service delivery visit (i.e., appointments/visits with any type of mental healthcare service provider). Health record notes for all mental healthcare visits will be reviewed in detail to identify all content related to sleep, physical activity or screen time assessments, discussions or recommendations for change. The complete text of each lifestyle-related clinic note will be de-identified for any patient-specific information before being transferred to our research database. Sex and mental health diagnoses will also be extracted from health records.

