# Statistical Plan

## Sample Size Determination

The size of the study sample will be determined by the number of eligible youth contacts (with 1Call1Click or directly to the research team). Our pilot study approached 5-10 youth/week via 1Call1Click with 25% enrolling, providing an expected 400-800 potential and ~100-200 enrolled participants over 18 recruitment months. Complete data for 122 youth would provide 80% power to detect a 3.4 point difference in emotional health (Strengths & Difficulties Questionnaire), equivalent to the 19.5% improvement observed in our 3-month pilot study.

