### Efficacy Outcomes

The primary outcome is youth emotional well-being as measured by the Strengths & Difficulties Questionnaire (SDQ^34^). We define a clinically significant improvement as a score decrease of 15%, with the reduction occurring only when participants have engaged with the intervention. This change is just less than 1/2 of the SDQ improvement observed after 6 months of specialist community mental health services^43^. We do not expect HELP benefits to be equivalent to traditional mental health interventions. However, we believe that the ability to improve emotional health half as well as traditional therapies would provide a meaningful and important change. In our pilot study, SDQ scores improved by 19.5% in 3 months among engaged youth. We will evaluate the change in SDQ from baseline to 6 months in a repeated measures model adjusted for age (years), gender, intervention adherence, type of mental health concern (e.g., anxiety, depression, etc. as documented during 1Call1Click intake), and support referral (community or specialist services recommended by 1Call1Click intake staff). The impact of sex will be investigated if participants include a sufficient number of youth who do not identify as the gender aligned with their sex.

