Secondary efficacy outcomes are measures of readiness for behaviour change (i.e., stage of change) and sleep, physical activity and screen time behaviour. Behaviour change theory emphasizes that individuals move through a series of stages, with the most effective intervention differing for each stage. HELP supports youth in all stages of change. “Learn” targets youth not yet considering behaviour change. “Pro’s and Con’s” guides youth to address their ambivalence towards change. “Goals” provide step-by-step plans so youth can act on their intention to change behaviour. “Roadblocks” support the maintenance of recent behaviour changes. Paired t-tests will examine participants’ stage of change at enrollment and 6 months to assess whether HELP enhanced their readiness for behaviour change. Modeling how the behaviour change stage differs, with adjustments for age, gender, intervention adherence, type of mental health concern and support referral, will assess whether HELP similarly impacts behaviour change among all youth. The same analyses will be completed for each behaviour outcome with stage of change at 6-months a mandatory variable as theory indicates that achieving Stages 3 to 5 is required for behaviour change to occur (Stages 1 & 2 are moving toward the decision to change behaviour).

A repeated measures model of the primary and secondary outcomes will evaluate changes between study groups, comparing changes occurring during intervention access to changes when the intervention is not available. Changes between the 0 and 6-month assessments for youth randomized to immediate intervention access and between the 6 and 12-month assessments for youth randomized to the wait list group will evaluate HELP e-intervention efficacy. Differences between the 6 and 12-month assessments for youth randomized to immediate intervention access will evaluate the sustainability of the intervention effects. Differences between the 0 and 6-month assessments for youth randomized to the wait list group will evaluate changes in study outcomes over time without the HELP e-intervention. Comparisons between 0 and 3-month and 3 and 6-month outcomes will determine the required length of the HELP e-intervention for optimal outcomes. All models will be adjusted for age, gender, intervention adherence, type of mental health concern and support referral.

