### Healthcare System Outcomes

Measures of youth mental healthcare system utilization will be compared between the intervention and wait list control participants. Independent t-tests will compare the number of system contacts, number of service delivery visits and length of service delivery visits for each timeframe (with/without intervention access). Chi-square statistics will compare categorical variables (type of system contacts, type of service delivery visit, professional seen, purpose of service delivery visit) between the intervention and control participants for each timeframe. Linear regression models will compare these outcomes between the intervention and control participants, adjusting for demographic variables (age, sex, mental health concern). Repeated measures models will evaluate the pattern of changes to mental health service use throughout study participation.

The frequency of lifestyle support during mental health services will be evaluated using mixed methods. Each comment in the research database will be coded to indicate the focus (assessment, discussion, recommendation), content and information conveyed by the comment utilizing the same procedures and coding framework developed during our retrospective chart review^44^. Descriptive statistics (frequency tabulations, means or medians (variance) as appropriate) are then used to summarize the data. We will also analyze these data qualitatively, using an inductive approach (no preconceived coding framework). Independent analyses of the qualitative data will be completed by two members of the research team to summarize the lifestyle-related discussions during patient visits. Inductive analyses will begin with data immersion, reading/re-reading the extracted comments. Analytical notes and key phrase identification will identify concepts and enable initial code creation (NVivo nodes). Analyses, interpretation and revisions will continue throughout the analytical process. Data will be interpreted relative to understanding lifestyle needs and counselling for these youth. Key findings will be reviewed separately by age group (12-14, 15-17), sex and type of treatment to identify any trends suggesting that lifestyle needs vary systematically.

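### The healthcare-use regressions omit intake support referral, a baseline covariate that every efficacy model already requires, at a nil-to-modest cost in precision on research question 4

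*Protocol*

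**What the plan says.** Efficacy Outcomes adjusts the primary SDQ model for age, gender, intervention adherence, type of mental health concern and "support referral (community or specialist services recommended by 1Call1Click intake staff"). The same section closes: "All models will be adjusted for age, gender, intervention adherence, type of mental health concern and support referral".

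Healthcare System Outcomes is a separate section with its own list. It compares contacts, visits and visit length by unadjusted t-tests and categorical measures by chi-square tests. Linear regression then compares the arms, "adjusting for demographic variables (age, sex, mental health concern"). Support referral is absent and no reason is given. A further sentence adds that "Repeated measures models will evaluate the pattern of changes to mental health service use throughout study participation", with no covariates named.

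These analyses serve research question 4, which asks whether youth engaging with HELP "utilize fewer mental healthcare resources, during and for 1 year following RCT participation". The chart review described under Study Assessments records, for each service delivery visit, "number, type (e.g., community provider, peer support, outpatient, day treatment, inpatient"), together with the purpose, the professional seen and the length.

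**The concern.** Support referral is the intake recommendation on which kind of service a youth should use. The outcomes of research question 4 are how much service the youth used and of which kind. If the variable is worth adjusting for when the outcome is an SDQ or sleep score, it is at least as natural a predictor of visits. The shorter list is not purely demographic either: it keeps one clinical variable, mental health concern, and leaves this one out.

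What is at stake is precision. Predictable variation between community- and specialist-referred youth stays in the residual, so the interval for the effect on service use may be wider than it needs to be.

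**Working it through.** **1. The lists side by side**

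| Covariate | Efficacy models | Healthcare-use linear regression | Healthcare-use repeated measures |
|---|---|---|---|
| Age | yes | yes | none named |
| Gender or sex | gender | sex | none named |
| Mental health concern | yes | yes | none named |
| Intervention adherence | yes | no | none named |
| Support referral | yes | no | none named |

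Adherence arises after randomization, so leaving it out of the service-use regression is defensible. That reason does not apply to a recommendation recorded at intake before randomization.

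**2. The plan's own power figure**

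Sample Size Determination states: "Complete data for 122 youth would provide 80% power to detect a 3.4 point difference in emotional health". No SD is given, so the figure can only be inverted. With 61 per arm (1:1 assumed) and two-sided 5%:

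SD = 3.4 / [(1.960 + 0.842) × √(2/61)] = 6.70.

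This is plausible but cannot be confirmed, and it concerns the SDQ only. No power or sample size is given for healthcare use. N = 122 is borrowed below as a working size.

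**3. Cost of the extra parameters**

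Assume the current regression has age, sex and three indicators for concern. At N = 122 the variance of the treatment effect is then inflated by:

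- one added parameter: 1 + 1/(122 − 9) = 1.009;
- two added parameters (three-level referral): 1 + 2/(122 − 10) = 1.018.

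The net variance factor is (1 − partial R²) × 1.018. Break-even is at partial R² = 1 − 1/1.018 = 0.018.

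**4. How much referral might explain**

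Every input here is assumed. Let a fraction p be specialist-referred, with mean visits m_c = 3 (community) and m_s (specialist), and negative binomial counts with variance m + m²/k.

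R² = p(1−p)(m_s − m_c)² / [p(1−p)(m_s − m_c)² + (1−p)(m_c + m_c²/k) + p(m_s + m_s²/k)]

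The range taken is p = 0.3 or 0.5, m_s/m_c = 1.5, 2 or 3, and k = 0.5 or 1.

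- Lowest (p = 0.3, 1.5-fold, k = 0.5): 0.4725 / (0.4725 + 28.2) = 0.016.
- Highest (p = 0.3, 3-fold, k = 1): 7.56 / (7.56 + 35.4) = 0.176.

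**5. Net gain at N = 122, with two added parameters**

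Power is shown from an assumed 80% without referral: Φ(2.802/√factor − 1.960).

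| Partial R² | Variance factor | Effective N | Power |
|---|---|---|---|
| 0 | 1.018 | 120 | 79.3% |
| 0.02 | 0.998 | 122 | 80.1% |
| 0.05 | 0.967 | 126 | 81.3% |
| 0.10 | 0.916 | 133 | 83.3% |
| 0.15 | 0.865 | 141 | 85.4% |
| 0.176 | 0.839 | 145 | 86.4% |

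The last two rows are the 3-fold case at k = 1 (p = 0.5 and p = 0.3). Their effective sample gains are 1/0.865 = 1.16 and 1/0.839 = 1.19.

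**6. Simulation check**

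Overdispersed counts were simulated with N = 122, half specialist-referred, a mean of 6 visits in the lower group, and variance m + a·m² with a = 0.5 or 1. One covariate was added.

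- 1.5-, 2- and 3-fold differences gave R² of 0.04–0.07, 0.09–0.15 and 0.17–0.27.
- The standard error of the treatment effect fell by 1–2%, 4–6% and 7–14%.
- The estimate was unbiased with and without the covariate.

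The upper figures come from a = 0.5, which is less overdispersion than in step 4. There a 3-fold difference would be worth 1/0.864² = 1.34 in effective sample.

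**7. Marginal against partial R²**

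The R² values in steps 4 and 6 are for referral alone. The regression already contains mental health concern, on which the recommendation plausibly depends, so the partial R² is likely to be smaller.

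**The case against.** The two sections cover different outcomes from different sources, and the service-use list differs in other ways as well: sex in place of gender, and no adherence. Sex and diagnoses are extracted from the chart along with the visits, so the list may have been chosen deliberately for chart-based analyses. Adding a prognostic covariate to a non-primary outcome can be called a matter of preference. This stands to the extent that the two sections do not contradict each other: the efficacy sentence about all models closes its own section and need not reach further. It does not explain why a pre-randomization variable that the trial already needs is left out of a list that the protocol itself closes.

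Three stronger readings are tempting and not supported:

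- **Bias.** A reader might infer that an imbalance in referral could pass for an effect of HELP. Chance imbalance in any unadjusted baseline variable is already allowed for in the type I error, and the simulated estimate was unbiased either way.
- **Free precision.** Referral is set by 1Call1Click staff, yet "additional youth may be recruited through our two secondary recruitment options", so some youth may have no value. A level for them makes referral a three-level factor, and at the low end the gain does not exceed the cost. That the value is collected is inferred from its place in the efficacy models; the data-collection sections do not list it.
- **Dropped from all service-use models.** The omission is explicit only for the linear regression. The repeated measures models name no covariates at all.

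It is also fair to object that service use comes from chart review, so 122 questionnaire completers is not the protocol's sample size for this question.

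**Conclusion.** The point holds as a minor one about efficiency. The covariate list for the linear regressions of healthcare use omits intake support referral, which the efficacy models require and which plausibly predicts the number and type of visits. The comparison of arms remains valid.

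The loss of precision on research question 4 is about nil if referral's partial R² is 0.02 or less. It reaches roughly 15–20% of effective sample size if specialist-referred youth have about three times the visits and k is near 1. Less overdispersed counts would raise that ceiling, and overlap with mental health concern would lower it. The specialist share, the visit ratio, the mean, the dispersion and N = 122 for this outcome are all assumptions. That referral predicts service use is reasoning from how the variable is defined; the protocol gives no data on it.

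**What to change.** In Healthcare System Outcomes, change the covariate list for the linear regressions to *age, sex, mental health concern and support referral*. Define support referral as the recommendation recorded at 1Call1Click intake before randomization, not the services later received, and give youth recruited without such an intake their own level. Name the same list for the repeated measures models of service use. If the omission is deliberate, state the reason instead.

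The cost is one phrase and one or two model parameters, about 1–2% of variance at N = 122. No further participants are needed, and no new data beyond what the efficacy models already call for. The rule for youth without an intake value is needed for the efficacy models in any case.

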# Background Information and Scientific Rationale

## Background and Rationale

### The Problem

500,000 Ontario youth (20-30%) have ≥ 1 mental health disorder^1^, 75% without specialist treatment^1^, compromising the timely care essential for optimal outcomes. 28,000 Ontario youth wait 8-30 months for care^2^. 200,000 youth have no access to care. Youth make 1.35 million out-patient and 70,000 emergency mental health visits/year. Youth suicidal ideation/self-harm doubled in 3 years^2^ prior to the pandemic. While mental health emergency hospitalizations skyrocket among youth; other causes are declining or stable. The critical shortage of mental health clinicians compounds increased treatment demand.

Youth are immersed in social media, doing little physical activity^3^ – lifestyle choices impacting their physical and mental health. Only 17.5% of Canadian youth meet sleep, physical activity and screen time guidelines^4^, and we know that meeting healthy lifestyle guidelines is associated with enhanced mental health. Achieving physical activity recommendations in grade 5 decreased adolescent mental illness risk by 47%^5^. Meeting screen time guidelines decreased mental health risk by 25%^5^. Each additional lifestyle guideline met further reduced mental health risk^6^.

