**Rationale for Lifestyle Change interventions**

Youth are immersed in social media and doing little physical activity – poor lifestyle choices that impact their physical and mental health. Reviewing 102 health records of youth (50♀) receiving specialist support at CHEO we found few met criteria for major psychiatric diagnoses. Nevertheless, during the first two visits over 90% were counselled about changing sleep, physical activity and/or screen time. That mental health specialists are addressing the need for lifestyle change in the first visits with virtually all adolescents is evidence of the importance of lifestyle behaviour assessment/change as part of mental health treatment. There is a need to study lifestyle change intervention effectiveness in youth with mental illness because such interventions offer affordable, enjoyable, rewarding, and stigma-free treatment options that have no/few side effects/complications, and can be done individually or with family^14^. Healthy behaviours and moods spread through social networks, providing an opportunity for multiplier effects of lifestyle change on other family members, friends and neighbours^23^.

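### Research question 5 compares lifestyle support between HELP and control youth, but the analysis fixed for that outcome is descriptive and never split by randomised arm

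*Protocol*

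**What the plan says.** The question is comparative. Protocol, Research Questions, item 5 asks whether professionals supporting HELP youth "provide lifestyle behaviour support less frequently than for youth who do not receive the intervention". Study Objectives likewise lists the effect of HELP on the need for professional lifestyle support as something the trial will evaluate.

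The hypotheses in the same section make two statements that bear on each other. One is that "youth engaging in the HELP e-intervention will require fewer youth mental health supports". The other is that these youth, "when supported will be less likely to require treatment directed at lifestyle behaviours".

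The outcome comes from visit notes. Study Assessments says "Health record notes for all mental healthcare visits will be reviewed in detail to identify all content related to sleep, physical activity" or screen time.

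The analysis is in Healthcare System Outcomes, second paragraph. Each comment is coded for focus and content. Then "Descriptive statistics (frequency tabulations, means or medians (variance) as appropriate) are then used to summarize the data". An inductive qualitative analysis follows, and finally "Key findings will be reviewed separately by age group (12-14, 15-17), sex and type of treatment", to look for trends in lifestyle needs.

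**The concern.** A between-arm question needs a between-arm analysis. The protocol does not simply leave this one open for a later plan. It gives the outcome its own paragraph and its own methods, and those methods describe the content of notes without contrasting HELP with control. A team following the text would produce a description of lifestyle counselling across the sample and leave a stated objective unanswered.

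The likely repair is an unplanned comparison added at reporting, and the wording of the hypothesis points that comparison towards youth who were seen. Being seen happens after randomisation, and the protocol expects HELP to make it less common. The two groups of youth seen would then no longer be protected by randomisation.

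**Working it through.** **1. Question against analysis**

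| Outcome | Question | Analysis stated in Healthcare System Outcomes | Split by arm? |
| --- | --- | --- | --- |
| Service use (question 4) | HELP versus no HELP | t-tests, chi-square and linear regression on contacts, visits, visit length, type, professional and purpose | Yes |
| Lifestyle support (question 5) | HELP versus no HELP | Comment coding, descriptive statistics, inductive qualitative analysis; review by age group, sex and type of treatment | No |

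The outcomes listed in the first row do not include lifestyle content. Visit purpose, which Study Assessments illustrates as assessment or counselling, does not capture it. Type of treatment in the second row reads most naturally as the kind of mental health treatment, not the trial arm.

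**2. Are the data there?** Yes. Consent to health-record evaluation is an inclusion criterion. Expected Duration of Participation and Study Assessments provide for chart review over 18 months from enrolment, covering every visit and all lifestyle content in the notes. Controls get HELP only between months 6 and 12, so months 0-6 give a clean randomised contrast.

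**3. What restricting to youth seen can do.** The protocol gives no figures for this, so all inputs here are assumptions, in three scenarios. Half of the youth are severe, are always seen, and receive lifestyle support with probability 0.95. The other half are mild and receive it with probability 0.80 if seen. HELP changes only *m*, the share of mild youth who are seen. It has no effect on support once a youth is seen.

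- Seen = 0.5 + 0.5*m*
- Supported per randomised youth = 0.5 × 0.95 + 0.5 × *m* × 0.80 = 0.475 + 0.40*m*
- Supported among those seen = (0.475 + 0.40*m*) / (0.5 + 0.5*m*)

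| Scenario | *m* | Seen | Per randomised youth | Among those seen |
| --- | --- | --- | --- | --- |
| Control | 0.90 | 0.95 | 0.835 | 0.835/0.95 = 87.9% |
| HELP, moderate drop in visits | 0.60 | 0.80 | 0.715 | 0.715/0.80 = 89.4% |
| HELP, large drop in visits | 0.30 | 0.65 | 0.595 | 0.595/0.65 = 91.5% |

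Among those seen, the HELP arm looks slightly worse, against the hypothesis, only because milder youth have dropped out of the comparison. Per randomised youth, support falls by 12 or 24 percentage points (83.5 − 71.5; 83.5 − 59.5). That fall is wholly due to fewer youth being seen. Neither measure alone shows what clinicians do at a visit.

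**The case against.** **A protocol may leave the test for a non-primary outcome to the analysis plan, and a list of subgroups does not rule out tabulation by arm.** Both statements are true, and an analysis plan that is not shown could add the comparison. But the protocol sets out methods for this outcome, and they do not match its question. The paragraph directly before it names the arm comparison for service use, so the contrast is in the protocol's own text.

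**The question is about youth being supported, so counting zero for the unseen changes it.** This stands in part. The per-youth count combines how often youth are seen, which is question 4, with what happens when they are. It could fall while clinicians behave identically, as the working shows. For that reason the per-visit measure must be reported beside it.

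**Stronger readings that the documents do not support:**

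- *The trial cannot answer question 5.* It can: allocation, visits and lifestyle content are recorded for all participants. The defect lies in the stated analysis.
- *A conditional comparison is at its ceiling,* because in the earlier chart review "during the first two visits over 90% were counselled about changing sleep, physical activity and/or screen time". The hypothesis is a fall, and a high control rate leaves room for one. As a check, assume 61 per arm (122/2), two-sided 5%, 80% power and a normal approximation for two proportions. From 95%, a drop to about 78% is detectable, or to about 68% if only half of each arm is seen. Those chart figures are also ever-counselled proportions, whereas the question concerns frequency.
- *Few participants will have visits,* because "28,000 Ontario youth wait 8-30 months for care". That is a province-wide background figure. Recruitment includes youth already in care, and community and peer contacts are counted.
- *A definite share of lifestyle-support workload would be missed.* Any such figure comes entirely from the numbers assumed to be seen, and visits are already compared between arms under question 4.

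**Conclusion.** The concern holds as a mismatch between question and analysis. The protocol poses research question 5 as a HELP-versus-control comparison and then fixes a descriptive and qualitative analysis with no split by arm. This rests on the text alone and needs no assumption beyond reading type of treatment as clinical treatment.

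The selection point also holds: a comparison limited to supported youth conditions on an event after randomisation that the protocol itself expects HELP to change. Its size cannot be derived from the documents. The shift from 87.9% to 89.4% or 91.5% among those seen only illustrates direction under assumed inputs. No stated figure of the trial changes, and the primary outcome is unaffected.

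**What to change.** In Healthcare System Outcomes, state that:

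1. The outcome for research question 5 is the number of visits containing a lifestyle assessment, discussion or recommendation, counted per randomised youth, with zero for youth who have none.
2. It is compared between randomised arms over months 0-6, before controls have access. Months 0-18 are reported as immediate versus delayed HELP.
3. Lifestyle content per visit among youth seen is reported by arm beside it, as a supportive measure, with the caveat that those seen are a group selected after randomisation.

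In Research Questions, reword the hypothesis so that it no longer rests only on youth who are supported. The planned coding, qualitative analysis and review by age group, sex and type of treatment can stay.

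The cost is wording in two sections. No new data or participant burden is needed, provided each coded note keeps its study ID and visit date so that it can be assigned to an arm and a period. The downside is interpretive: the per-youth count mixes visit volume with visit content, so it has to be read together with the per-visit measure and the question 4 results.
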